#### Sarcopenia

Muscle mass will be measured with bioelectrical impedance analysis (BIA; Seca Medical Body Composition Analyzer 515, Seca, Hamburg, Germany). Four-meter usual gait speed will be used as surrogate parameter for function and handgrip for muscle strength. Handgrip strength will be assessed with a Jamar hydraulic hand dynamometer (Sammons Preston Rolyan, Bolingbrook, IL, USA). All measurements will be done according to the EWGSOP2 recommendations [12].

#### Physical performance

Physical performance will be assessed via the Short Physical Performance Battery (SPPB), which is a brief performance battery based on a set of functional tasks related to the lower limbs [34]. Additionally, a one leg stand is performed for 10 s.

#### Changes of gait characteristics

In a subsample of participants, gait will be investigated with the GAITRite system (Rölke Pharma GmbH, Hamburg, Germany) as it also has very good psychometric properties demonstrated and is the gold standard for measuring gait characteristic [35].

#### Health-related quality of life (HRQoL)

HRQoL will be measured with the EURQOL (EQ-5D). The sum score and visual analogue scale (VAS, 0–100) will be determined [36] that is widely used in medical research.

#### Subjective health

Self-rated subjective health (SRH) will be obtained by a single question “In general, how would you rate your current health status?” with five response options: “very good,” “good,” “fair,” “bad,” or “very bad.”

#### Activity (actigraphy)

Objective Physical Activity (PA) will be assessed by actigraphy using the activPAL system (PAL technologies, Glasgow, UK). The activPAL system provides information on body postures e.g., sitting, lying, and walking. This information enables to obtain sedentary as well as physical activity behavior [37].

### Cognitive function

In order to test cognitive function and to ensure that all participants are able to comply with the study protocol and to provide informed consent to the study the Mini Mental State Examination (MMSE), as a part of the CERAD (Consortium to Establish a Registry for Alzheimer’s Disease), neurophysiological test battery will be applied. The MMSE is a widely used screening tool that provides a brief, objective measure of cognitive function and is one of the best validated tests of cognitive function among the elderly [38]. The MMSE cut-off score of < 24 will enable the participants to follow the CaF training, which is a cognitive-behavioral oriented training.

Furthermore, the Trail Making (Versions A and B) of the CERAD will be used to monitor executive function and cognitive flexibility [39].

### General psychological status

#### Depressive symptoms

In order to assess depressive symptoms, the Geriatric Depression Scale (GDS-15) will be used. GDS is appropriate for the age group in this project [40, 41].

#### Perceived stress

Perceived stress will be assessed with the general perceived stress scale (PSS). PSS is used for assessment of sub-chronic life stress in adults [42, 43] and is validated for older adults as well [44].

We will use the 10-item version as a global assessment of perceived stress, with which the sum scores could be assessed on a scale between 0 and 40. Higher sores indicate higher perceived stress with cutoff points 0–15 reflecting low and 15–40 high perceived stress for older adults aged 70 years or older [42].

Furthermore, perceived stress at saliva sampling time points will be rated on 5-point Likert-type scales. This self-reported questionnaire was previously used in research at the Chair of Health Psychology.

#### Anxiety

Anxiety will be operationalized with the Geriatric Anxiety Scale (GAS) [45]. GAS is a self-reported screening and assessment tool designed specifically for older adults. The GAS contains 25 scored items and 5 additional ones addressing specific areas of concerns often reported by older adults (for clinical application). Different components of anxiety, somatic, cognitive, and affective domain will be recorded in GAS scale. In this study, the German version of GAS (GAS-G) will be assessed [46]. Higher sum score indicates higher anxiety.

### Concerns about falling (CaF)

As a measure of CaF, the FES-I scale will be used, which is a 16-item questionnaire related to CaF during basic and more demanding daily activities among independent, community-dwelling older adults. The validated German version of the FES-I will be used [47]. In addition, to investigate the behavioral consequences of CaF the FES-IAB currently validated by Kruisbrink et al. [48], and to assess the perceived control of falling, the translated Updated Perceived Control over Falling Scale (UP-COF) scale will be used [49].

### Stress and stress-related pathophysiological processes

#### Stress system activity

Chronic stress has profound effects of the two main stress systems, HPA axis and SNS. We will assess basal activity of the HPA axis and SNS using non-invasive, at-home saliva samples measuring salivary cortisol for the HPA axis and salivary alpha-amylase (sAA) for the SNS, respectively, as for example documented in [name] et al. [50]. Based on our extensive experience with saliva sampling in home contexts [50–52], we will use the following procedure to ensure sufficient adherence of participants to the protocol. At first, an in-person explanation and practical instruction of the saliva sampling procedure will be conducted during the appointment. Second, a detailed set of written instructions will be provided along with a brief questionnaire asking participants for sampling times for reference at home. Participants will be asked to take three saliva samples at the following time points over two consecutive days: upon awakening, 30 min after awakening and at bedtime, for a total of six saliva samples. Participants are then asked to send all collected samples to the joint laboratory of the Chair of Health Psychology and the IBA using the pre-stamped envelope. Both, cortisol and sAA, are sufficiently stable at room temperature for this procedure [52]. Cortisol will be measured using a commercially available chemiluminescence immunoassay (Tecan, Hamburg), and sAA will be measured by an enzyme kinetic assay as described previously [50] using reagents by Roche Diagnostics (Mannheim).

#### Systemic inflammation

To assess systemic low-grade inflammation, we will take one blood sample at an appointment at the IBA using EDTA Vacutainers (BD, Heidelberg). As biomarker of stress-related pathophysiological processes, plasma concentrations of CRP, IL-6, and TNF-alpha will be assessed, and as a marker of anti-inflammatory activity, IL-10 will be measured with reagents by R&D Systems (Minneapolis, MN, USA).

#### Intracellular inflammatory activity

To obtain a more direct indication of the innate immune system’s contribution to systemic inflammation, gene expression of interleukin-1beta (IL-1beta), IL-6, IL-10, and I-kappa B will be analyzed. Therefore, RNA will be transcribed into cDNA, and gene expression analyses will then be performed according to standard procedures using real time quantitative RT-PCR as previously described, using primers and reagents from Life Technologies, or ThermoFisher [50, 53].

### Intervention

The intervention group will take part in a 16-week multicomponent exercise intervention.

During the initial 4 weeks, training sessions will take place twice a week, with supervised 60-min sessions at the IBA, where the participants will be familiarized with the components of the program. From week 5 to week 16, one supervised session per week will be provided at the IBA, and two 30-min sessions will be completed by participants as an unsupervised home program. An adherence rate of 75% in the intervention sessions will be considered as successful participation [54–57].

The multicomponent intervention will contain elements of gait, balance, and strength exercise to improve physical function and elements of the “Matter of Balance” program to reduce CaF [58]. The time points and frequency of the different exercise and behavioral components in the intervention are summarized in Table 2 and described in detail in the following.

**Table 2 Tab2:** Time points and frequency of the intervention components

	**Month**				**Total**
**Intervention components**	1	2	3	4	
Strength training	2	2	1	1	6
Challenging balance training	2	2	2	2	8
Functional training		1			1
Gait training	1		1		2
Body awareness		1		1	2
CaF training		1	2	1	4
Home program	1			1	2

### Strength training

The strength training includes progressive strength exercises for upper and lower body and stretching exercises. The focus is on lower limb strengths and strength training will adhere to the effective Otago exercise program [59]. This program was repeatedly been shown to reduce falls in older adults. In short, the single exercise will include, e.g., wide leg squats knee extension, leg curl, and hip extension. All exercises will be conducted in two sets starting with five repetitions and increasing up to 10 repetitions. Participants will wear individually adjusted ankle weights based on the results of the self-rated exhaustion (Borg scale). As previously demonstrated, this sequence of exercises is successful in increasing strength in older adults [54].

### Challenging balance training

Challenging balance training will include static and dynamic balance exercise with progression, e.g., tandem stand and tandem walk. The increasing demands on balance control will involve reducing the amount of support. Initially, participants will hold onto a chair with both hands, then progress to using one hand, fingertips, and ultimately zero support. Additionally stable and unstable ground (e.g., foam mats) may be used as appropriate. The balance exercises will be tailored to each individual’s level.

### Gait training

Different gait components, e.g., step widths and step lengths, will be included in the gait training. The gait exercise will also include different rhythmical, spatial, and temporal components, as well as a dual task condition, e.g., walking and talking, and combination of gait and arm movements [54].

### Functional training

Functional training will include getting up from the floor by using the backward chaining methods [60].

### Body awareness exercise

Body awareness exercise will include body orientation practice. For instance, how can I attain an object without compromising my balance and disbalancing the positions of my center of mass and pressure? [54].

### CaF training

CaF training will include elements of the effective “Matter of Balance” training [58]. The “Matter of Balance” intervention is a cognitive-behavioral oriented training including goal setting elements for behavioral changes, e.g., to increase physical activity or integrate exercise elements of the home program into the individual daily routine. Misconceptions regarding the risk of falling, attitudes towards falls, thoughts, and CaF as well as negative and positive cognitive patterns, along with possible environmental hazards that could lead to falls will be examined. The elements include assessing daily situation with CaF with regard to thoughts, physiological symptoms, and behavioral aspects. Goal setting is to reduce CaF in these situations. In addition, self-efficacy regarding behavioral fall related aspects will be trained to reduce avoidance behavior in daily activities.

### Home program

Home program will be based on a brochure describing how to perform strength, balance, and gait exercises safely and regularly ([Online] Available from: https://www.gesund-aktiv-aelter-werden.de/service/mediathek/bewegung/sturzpraevention/ [Accessed 24 Nov 2023]) (https://www.gesund-aktiv-aelter-werden.de/service/mediathek/bewegung/sturzpraevention/). Materials from the “Bundeszentrale für gesundheitliche Aufklärung” could be regarded as usual care for fall prevention without exercise intervention. Participants will report the adherence to the home program in the intervention session, and further support will be elaborated for integrating the guidelines in the individual daily life.

### Sham control group

The sham control intervention will occur in the same frequency as the multi-component exercise intervention, over a 16-week period (as mentioned previously). Each session will contain a 40-min educational presentation and 20 min of light upper extremity stretching. In the SCG, the groups sizes will vary between 20 and 30 participants. As a fundamental aspect, the SCG will receive light stretching exercise and strength training of the upper extremities. Second part of the control intervention will be educational health lectures, as previously described before [61]. Topics of the educational and light stretching training sessions are detailed in Table 3.

**Table 3 Tab3:** Topics of the control intervention

*Domain*	*Topic*
**Exercises**	
Light stretching of upper extremities	Standardized stretching of upper extremities with instruction of the home program
Strength training of the upper extremities	Exercises for strength training of upper extremities
**Health lectures**	
Demographic changes	Challenges and chances of an older population
Aging	Challenges and chances for older adults (healthy aging, living space adaptation, care order, living will, crime prevention, senior networks)
Medical topics	Polypharmacy, interpretation of laboratory test results, first aid, gait
Cognitive training	Training of short-term storage and retrieval, the training of memory strategies for long-term storage, attention and changes in aging
Nutrition	Challenges and chances of nutrition in older population

Participants will also receive a home-based light stretching booklet, brochures in health lecture topics, and a summary of the entire course.

### Criteria for discontinuing or modifying allocated interventions {11b}

Criteria for discontinuing the intervention for a participant is an adverse event such as a fall or accident resulting in severe injuries (e.g., fractures), which permanently prevents their participation in the intervention.

### Strategies to improve adherence to interventions {11c}

For saliva sampling, which will be undertaken by the participants themselves, personal meeting includes explanation and practical instruction of saliva sampling procedure. A detailed set of written instructions and a brief questionnaire asking participants for sampling times for reference at home are provided at this first appointment at IBA. If saliva samples were not returned after certain time, close communication via phone calls will be applied. Participants receive personal reminder calls for the assessments and testing appointments, if desired.

The participants will be introduced to each other during the intervention sessions to enable social bonding to the program. Special efforts will be made to keep the participants of the SCG in the project by handing out birthday cards and celebrating Christmas at a special event together.

### Relevant concomitant care permitted or prohibited during the trial {11d}

Measurement of salivary cortisol may be influenced by various factors, such as tooth brushing, eating, drinking caffeinated beverages, and regular physical activity. Therefore, participants are asked to refrain from consuming anything (except drinking) water, smoking, chewing gum, and brushing teeth for at least 1 h prior to saliva sampling. Excessive physical activity influences inflammatory biomarkers in the body. Therefore, participants are asked to avoid excessive physical activity 24 h before.

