## Potential risks and limitations

Many factors are known to potentially influence saliva cortisol measurement, such as tooth brushing, eating, drinking caffeinated drinks, and ordinary physical activity. Therefore, participants should refrain from consuming anything (except drinking) water, smoking, chewing gum, and brushing teeth for at least 1 h prior to saliva sampling. The time points for saliva sampling are specified and explained in person. Participants might not always adhere to these requests, which might influence the results.

In this sample is a high proportion of comorbidity, which might influence concentrations of biomarkers in blood and saliva samples. Polymedication and intake of, e.g., beta blockers interfere with the function of the autonomous nervous system [64].

A large number of factors may influence PSS as well as cortisol concentration: age, sex, smoking, BMI, ever diagnosis of depression, ever diagnosed cardiovascular disease, time of day.

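### The pre-sampling rules leave out ordinary exercise, which the protocol itself says affects salivary cortisol, so recent exercise load at T1 can differ in degree between the arms

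*Protocol article*

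**What the plan says.** Section {11d} of the protocol article opens with the reason for the saliva rules: "Measurement of salivary cortisol may be influenced by various factors, such as tooth brushing, eating, drinking caffeinated beverages, and regular physical activity". The limitations section repeats the list as "such as tooth brushing, eating, drinking caffeinated drinks, and ordinary physical activity". The restrictions that follow cover eating, drinking anything but water, "smoking, chewing gum, and brushing teeth for at least 1 h prior to saliva sampling". Physical activity is not among them.

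Activity has a separate rule with its own reason. "Excessive physical activity influences inflammatory biomarkers in the body", and so "participants are asked to avoid excessive physical activity 24 h before". The sentence ends there: neither the blood draw nor the saliva sampling is named, and *excessive* is not defined.

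Four other places bear on the point:

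- **Timing.** The study procedure section places T1 after the intervention or control period and gives no interval from the last session.
- **Intervention group (IG).** From week 5 there is one supervised session a week, and "two 30-min sessions will be completed by participants as an unsupervised home program". The content is progressive strength work for upper and lower body, balance and gait. The CaF training and home program sections aim to build the home exercises into daily life.
- **Sham control group (SCG).** It meets at the same frequency, with light stretching and strength work for the upper limbs, and receives a home stretching booklet.
- **Samples.** Saliva is taken on waking, half an hour later and at bedtime on two consecutive days. Blood is drawn once, at an appointment.

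**The concern.** The protocol names an influence on one of its outcomes and then sets rules that do not control it. Cortisol is said to respond to ordinary activity. The saliva restrictions ignore activity, and the 24 h rule reaches only excessive activity and is justified by inflammatory markers.

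This would be a small wording matter if activity were unrelated to allocation. Here exercise is part of what is randomised. Before the programmes start, any habitual exercise is unrelated to allocation. At T1 the arms may differ in how hard they have recently exercised, because their programmes differ. The between-arm change from T0 to T1 in a biomarker could then combine a lasting effect of the intervention with the short-term effect of the latest session. Objective 2 asks about the lasting effect, and Objective 3 builds on the same changes to judge which comes first, lower CaF or lower inflammation.

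**Working it through.** The protocol states no figure that bears on this point, so the check sets its statements side by side and then bounds how often a session could fall close to sampling.

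**Step 1. Stated influence against stated rule**

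- Salivary cortisol: the named influence is regular or ordinary activity. The one-hour rule does not mention activity. The 24 h rule covers only excessive activity and does not mention saliva. The influence is not controlled.
- Blood markers: the named influence is excessive activity, and excessive activity is restricted. Rule and reason agree, apart from the missing definition and the unnamed sampling.
- Alpha-amylase: no statement about activity either way.

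**Step 2. Would a programme session be barred?** A 60-minute class or a 30-minute home session prescribed by the trial would not naturally be read as excessive, so the rule as written allows one on the day of sampling or the day before.

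**Step 3. How often could that happen?** Inputs: weeks 5 to 16 have 1 supervised + 2 home = 3 sessions a week (intervention section). Assumptions: three different days placed at random in a 7-day week, and a pattern that carries on into T1 sampling.

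- A given day contains a session: 3/7 = 0.43.
- At least one of two consecutive saliva days contains a session: 1 − (4/7)(3/6) = 1 − 0.29 = 0.71.
- With only one session a week: 1/7 = 0.14 for a given day and 2/7 = 0.29 for two days.
- If the last session was well before T1 and home exercise had stopped: 0 for both.

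The protocol does not say which case applies.

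**Step 4. Which samples are exposed?** There are 3 samples × 2 days = 6. Four are taken on waking or 30 minutes later, before any plausible session that day. The two bedtime samples can follow a same-day session, each with probability 0.43 under the three-session assumption. The morning samples are open only to carry-over from the day before. The 0.71 is therefore the chance that a window contains a session day, not the share of samples affected.

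**Step 5. Is the exposure one-sided?** No. The SCG meets at the same frequency and also has upper-limb strength work and a home booklet. What differs is type and load: the IG adds progressive lower-body strength, balance and gait work.

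**The case against.** The strongest reply has four parts.

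**Both arms exercise, and T1 follows the course.** A reader might infer that recent exercise affects the IG alone. The protocol does not support that, because the SCG has sessions at the same frequency and strength work of its own. Carry-over also needs either a short gap from the last session or continued home exercise, and neither is stated. This stands: the possible bias is one of degree and is not demonstrated. It does not remove the point, because a difference in load need not cancel between arms, and continued home exercise is something the programme aims for.

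**The blood-marker rule matches its reason.** A reader might extend the point with equal force to IL-6, TNF-alpha, CRP and gene expression. Nothing in the protocol says that an ordinary session shifts these a day later, so for blood the risk is only possible. This also stands.

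**Scheduling detail belongs in the full protocol and the participant instructions.** The article mentions detailed written saliva instructions that are not shown, so the missing interval alone would be no finding. The mismatch between the named influence and the published rule does not depend on those documents.

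**The outcomes are secondary and explored, and the limitations section already discloses the influence.** This is correct and limits the weight of the point. Disclosure, however, does not help separate a recent-session effect from a lasting one if time since last exercise is not recorded.

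**Conclusion.** The point holds in a limited form. The protocol says that ordinary activity influences salivary cortisol, and its pre-sampling rules do not restrict ordinary activity. Recent exercise load at T1 can therefore differ in degree between the arms and can enter the secondary biomarker comparisons for Objectives 2 and 3. The bedtime saliva samples are the most exposed, with possible next-day carry-over to the morning samples. The primary outcome, FES-I at T1, is unaffected.

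The chance that a random day contains an IG session runs from 0% if training has stopped to 43% if three sessions a week continue into T1 on different, randomly placed days. The protocol gives neither size nor direction for the effect of a session, so no bias can be calculated. An evenly spaced pattern such as Monday, Wednesday and Friday would put a session day in 6/7 = 86% of two-day saliva windows. A reader might take this as the extent of contamination, but four of the six samples in a window precede any same-day session, so it would overstate the exposure.

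The change is worth making because it is cheap and these biomarkers carry the project's overarching objective.

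**What to change.** In section {11d}:

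1. Reconcile *regular* with *excessive* activity, and add exercise to the pre-saliva restrictions.
2. State that the 24 h apply to the blood draw and to the saliva samples.
3. Set one minimum interval from the last programme, home or other exercise session, identical in both arms.
4. Record the date and time of last exercise on the existing saliva-time questionnaire and on the blood visit form.
5. Add a sensitivity analysis of the biomarker comparisons by time since last session. That time arises after randomisation, so this analysis supports the main comparison and does not replace it.

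The cost is instruction wording, one item on each form, and slightly less flexible T1 and T2 appointments. activPAL wear should not overlap the restricted period, because the restriction could lower measured activity, which is itself an outcome. The protocol version is dated March 2024 and data collection runs to the second quarter of 2025, so the change can still reach later visits. The date it takes effect should be recorded.
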